**Exploratory outcomes**

- Patient education/knowledge outcomes as measured at baseline and 6 months
- Comparison of EyeArt diagnostic results to DR diagnosis by an eye specialist when evaluated by both methods for each individual eye.

**Covariates:** clinic site, age, sex, prior screening history, clinical risk factors, social determinates of health, barriers to care, and diabetes knowledge and self-efficacy.

## STATISTICAL METHODS

**Sample Size and Power Calculations:** Based on historical data from participating SYH clinics, we determined that approximately 59% of patients completed diabetic retinopathy screening, we powered our study to detect an increase of at least 10% in retinopathy screening completion (59% in the standard of care group to 69% in the intervention group), and assuming an  $\alpha$  of 0.05 (significance) and a  $\beta$  of 0.8 (power), we estimated that the target enrollment to detect this difference is 722 participants (361 per arm) using a two independent sample Pearson  $\chi^2$  test. Accounting for up to 15% attrition from consent to study intervention (participants who agree to participate and consent via phone, and either do not keep their appointment or who at the clinic appointment decide to withdraw from the study), we estimated as many as 848 patients (424 per arm) would need to be enrolled to ensure adequate sample size. To assess secondary outcomes, we determined that among the patients who underwent retinal screening within the previous 12 months at the participating SYH clinics, 11% were diagnosed with diabetic retinopathy; therefore, based on a screening uptake increase of 10%, a corresponding 16% increase in diabetic retinopathy diagnosis is anticipated in the intervention arm. However, if after the initial refinement

phase of the project, it is determined that either a smaller or larger percent of the target population is currently completing DR screening, we will adjust the study enrollment accordingly, to ensure we will have sufficient statistical power to evaluate the anticipated 10% increase in screening uptake.

**Statistical significance and transformation of variables:** All statistical tests will be two-sided unless defined otherwise. Statistical significance will be set at  $p$ -value  $<0.05$ . Where distributional assumptions are necessary for the correct evaluation of statistical results, appropriate description, diagnostic evaluation, and (if required) transformation of variables will be carried out. In the event the parametric tests indicated are unable to be used, non-parametric versions will be used.

The primary analysis will compare diabetic retinopathy screening completion between the intervention group and the standard of care group. Logistic regression will be used to estimate intervention efficacy using treatment arm as the main exposure variable and the odds ratio (OR) including 95 % CI will be presented. Hosmer and Lemeshow's approach to purposeful selection of variables will be used for final model selection.

Secondary analysis will compare diabetic retinopathy screening results between treatment arms using the same logistic regression approach as the primary analysis. Missing treatment results will be classified in this analysis and no diagnosis.

**Exploratory analysis:** Exploratory analyses will be performed to assess relationships between screening completion, screening outcomes, social determinates of health, and clinical risk factors. Changes in patient education/knowledge outcomes will be assessed using difference in

differences analysis. These analyses will be used to identify items that are most strongly related to barriers and/or compliance, and be used to refine and guide future implementation strategies.

Additionally, where both EyeArt and ICD-10 codes are available, results will be compared and shared with EyeArt, however these results will not be generalizable as only results from participants in the intervention group who received ungradable or abnormal EyeArt results and who were examined by an eye specialist and had results returned to the SYH will be available for comparison.

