2. **Randomization.** Participants of the DRES-POCAI study will be randomized into two groups: usual care (receive a retinal screening by an optometrist) or intervention group (receive a retinal screening using a special camera and EyeArt® system, an autonomous AI-based DR screening). The randomization will occur after consenting and completing the surveys, prior to conducting the DR screening process. The study coordinator will guide participants through the randomization process using a "Randomizer" app on a tablet or touchscreen device. The participant will press a designated button on the app to initiate random assignment to either the Intervention or Control group. The assigned group will display clearly on the screen for the participant to see.

***Intervention components and procedures.*** The sequence of the study activities that should occur during the intervention includes the health education sessions, administration of surveys and DR screening (***SOPs Surveys, Diabetic Retinopathy Screening and Participant Education***).

1. **Administration of surveys.** Baseline and follow-up surveys will encompass the baseline and 6-month follow up surveys, including the following domains, a) diabetes knowledge and beliefs, b) diabetes self-efficacy and c) diabetes self-management. In addition, participants of the intervention group will be asked to also complete participant satisfaction and experience survey at the check-out visit and at the 12-months follow up when participants return for their annual DR screening using POC-AI. Surveys will be available in English and Spanish (**Appendix 6**).

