- **Surveys/Questionnaires:** Some of the questions we ask may make participants feel uncomfortable. Study staff will emphasize that they are not obligated to answer any questions that make them uncomfortable, and that they can skip any question or stop participation at any time. The staff will make note of the instances when this situation happened, will report to the study leadership and document in the eCRF.

- **Diabetic Retinopathy Screenings:** Participants assigned to the POC-AI group may experience discomfort during the DR screening, such as light flashes or eye strain. It's important to note that these potential discomforts are minimal and momentary. The staff will track and report on the participants that decline or withdraw from the study for this reason. The staff will document this situation in the participant's eCRF and report to study leadership. Additionally, participants will not undergo dilation for the POC-AI DR screening, only participant in usual care group. The DR screening is part of a participant's medical care. While abnormal results may cause concern or stress, participants will receive information and clarify that these results do not constitute a final diagnosis. The study staff will explain that the results of the screening are not the final diagnosis, and the results should be reviewed by their medical provider. The medical provider will review the results with the participant and discuss any recommended treatment plan, such as a referral to an eye specialist. Ultimately, it will be the participant's choice whether to proceed with additional tests or treatments to evaluate what was observed.

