#### 9.4.3 ANALYSIS OF THE SECONDARY ENDPOINT(S)

**Secondary Endpoint 1:** Early-stage DR diagnosis and treatment (H2.2)

**Measurement:** Diagnosis of DR.

**Scale:** Categorical (vtDR and mtmDR positive, vtDR negative and mtmDR positive, vtDR and mtmDR negative, ungradable).

**Analysis:** Chi-squared test or logistic regression will be used to compare screening completion rates between intervention and usual care groups. Regression covariates may include demographics and baseline clinical factors. Covariate selection will aim for a parsimonious model to achieve clarity and avoid overfitting. We will evaluate the intervention effectiveness across subgroups/categories by including a risk group classification variable in our models (to determine if there are differences in outcomes by group). If these risk groups are determined to confound the relationship between intervention and outcome, we will then stratify our analysis.

**Results Presentation:** Adjusted odds ratios with 95% confidence intervals will be reported.

**Assumption Checks:** When logistic regression is used, the data will be assessed for linearity, absence of multicollinearity, and influential outliers.

**Populations:** All enrolled participants will be included in the analysis.

**Missing Data:** Multiple deletion or imputation methods will be used to handle missing data depending on the pattern of missingness, e.g. if entire surveys are missing if missingness is driven by specific items or response groups in the survey, and/or if the data is missing completely at random. We have allowed for a 10% dropout/withdrawal rate between enrollment and intervention, and thus can use pairwise or listwise deletion of up to 10% of participants and still maintain adequate power for analysis.

**Outliers/Non-adherence:** Data outliers will be assessed to ensure they are not the result of data entry or measurement error. True data outliers will be handled either by trimming, adjusting the weight of the outliers, or by using robust regression techniques. Non-adherence will be addressed by analyzing data per-protocol in addition to intent to treat.

**Exploratory Endpoints:** Knowledge, Attitudes, Self-efficacy, and Patient Satisfaction (H2.3)

**Measurement:** Outcomes representing participant knowledge, attitudes, self-efficacy, and satisfaction with study participation.

**Scale:** Multiple outcomes will be explored and may include nominal, binary, or categorical data.

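### The exploratory difference-in-differences analysis of education/knowledge outcomes is unbiased but, for numeric outcomes, less precise than adjusting the 6-month value for its pre-randomization baseline

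*Combined protocol and SAP*

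**What the plan says.** The SAP's list of exploratory outcomes includes "Patient education/knowledge outcomes as measured at baseline and 6 months". Under Exploratory analysis it gives the method: "Changes in patient education/knowledge outcomes will be assessed using difference in" differences.

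Protocol 8.1 fixes the order of events: "The randomization will occur after consenting and completing the surveys, prior to conducting the DR screening process". Protocol 4.2 says the same. Protocol 8.1 also lists the survey domains at both times as "a) diabetes knowledge and beliefs, b) diabetes self-efficacy and c) diabetes self-management".

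Neither document defines a summary score. Protocol 9.4.3 says of these endpoints: "Multiple outcomes will be explored and may include nominal, binary, or categorical data".

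The SAP's covariate list ends with "social determinates of health, barriers to care, and diabetes knowledge and self-efficacy", but the difference-in-differences sentence does not refer to that list. No section says that a 6-month survey outcome will be adjusted for its own baseline value. ANCOVA appears only in the abbreviation list (protocol 10.3).

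**The concern.** With one measurement before randomization and one after, a difference-in-differences in complete cases is the between-arm comparison of change scores. It subtracts the baseline with a fixed weight of 1. Randomization already balances the baseline in expectation, so the subtraction removes no bias, and it adds noise whenever the baseline predicts the 6-month value less than one for one. A regression on baseline estimates that weight from the data instead.

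The stake is the width of the confidence intervals for the survey part of Hypothesis 2.3. No power calculation covers these outcomes. Both arms receive educational materials and follow-up education (protocol 6.1.1 and 6.3), so the contrast may be modest and precision worth having. The SAP also expects some missing surveys (Missing data), which would reduce the information further.

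**Working it through.** **The plan's own figure.** The only sample size in the documents is for the primary outcome: 59% against 69%, two-sided α 0.05, power 0.80, 1:1, Pearson chi-squared test. With the mean proportion 0.64, n per arm = [1.960·√(2·0.64·0.36) + 0.842·√(0.59·0.41 + 0.69·0.31)]² / 0.10² = 360.5, so 361 per arm and 722 in total. This reproduces the stated figure (power 80.06% at 361 per arm). It does not involve the survey outcomes. The documents give no SD, effect size or correlation for those.

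**Variances.** Let σ be the SD at both times and r the baseline to 6-month correlation. Per participant:

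- Change score: σ² + σ² − 2rσ² = 2σ²(1−r).
- 6-month value adjusted for baseline: σ²(1−r²).
- Ratio, adjusted to change: (1−r²) / [2(1−r)] = (1+r)/2.

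Equal variances affect only the size of the gain. With baseline SD σ₀ and 6-month SD σ₁, the change-score variance minus the adjusted variance is (σ₀ − rσ₁)², which cannot be negative. In large samples adjustment is therefore never less precise.

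**Numbers.** r is an assumption. Detectable differences are in SD units for 80% power: (1.960 + 0.842)·√(2/361)·√variance.

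| r (assumed) | Change-score variance | Adjusted variance | Ratio | Fall in standard error | Detectable difference, change → adjusted | Power when adjusted, where change score has 80% |
|---|---|---|---|---|---|---|
| 0.3 | 1.40 | 0.91 | 0.65 | 19.4% | 0.247 → 0.199 | 93.5% |
| 0.5 | 1.00 | 0.75 | 0.75 | 13.4% | 0.209 → 0.181 | 89.9% |
| 0.7 | 0.60 | 0.51 | 0.85 | 7.8% | 0.162 → 0.149 | 86.0% |
| 0.9 | 0.20 | 0.19 | 0.95 | 2.5% | 0.093 → 0.091 | 82.0% |

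A simulation of 3,000 trials with 361 per arm gave variance ratios of 0.640, 0.736 and 0.860 at r = 0.3, 0.5 and 0.7, against 0.65, 0.75 and 0.85 from the formula.

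The 361 per arm is borrowed from the primary analysis, because no 6-month survey response rate is given. The ratio and the fall in standard error do not depend on that number; the detectable differences do.

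**The case against.** The strongest reply is that this is a preference about efficiency. Difference-in-differences is unbiased under randomization, the SAP classes these outcomes as exploratory, and their stated use is modest: "These analyses will be used to identify items that are most strongly related to barriers and/or compliance". That stands. The protocol synopsis and section 3 do list the survey aims as secondary, but no sample size is attached to them.

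A second reply is that the plan may already cover the point. The SAP lists diabetes knowledge and self-efficacy as covariates, protocol 9.4.1 describes covariate-adjusted regression in general, and a change score adjusted for its own baseline gives exactly the same arm estimate as the regression proposed here. This cover is incomplete. Nothing attaches an outcome's own baseline to this analysis. The rule in protocol 9.3 that brings imbalanced characteristics into the models depends on baseline testing, which the SAP drops (General Approach).

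A reader might infer more than the documents support:

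- *That every participant has a baseline score.* This holds by design only. Participants are told that "they can skip any question or stop participation at any time", and no score is defined.
- *That the sentence covers self-efficacy.* It names education and knowledge. Self-efficacy is a survey domain and part of Hypothesis 2.3, so including it is an inference.
- *That this is the only between-arm analysis of Hypothesis 2.3.* It is the only method named specifically for changes in survey outcomes, but the general rule in protocol 9.4.1 could also apply.
- *That the gain is large and free.* At r = 0.9 it is 5% of the variance. The figures apply to numeric outcomes. For binary items, baseline-adjusted logistic regression gives a conditional odds ratio, a different estimand from a difference in changes of proportions. For nominal items neither approach applies directly.
- *That regression on baseline has no drawback.* In its simple form it uses only people with both values, and missing surveys are expected.

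**Conclusion.** The point holds as a loss of efficiency in an exploratory analysis. It is not a validity error. For numeric education/knowledge outcomes the planned method gives wider intervals than the collected data allow. Adjusting for baseline would cut the standard error by about 19% at r = 0.3, 13% at 0.5, 8% at 0.7 and 2.5% at 0.9.

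The sizes rest on equal variances at the two times and on a correlation that the documents do not give. The direction rests only on the baseline being measured before randomization, which the protocol states, and on large-sample theory. The primary analysis and its sample size are not touched. This is a worthwhile improvement of low urgency.

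**What to change.** In the SAP's exploratory analysis:

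- Define the education/knowledge summary score or scores.
- For numeric summaries, make the between-arm analysis a regression of the 6-month value on arm, its baseline value and clinic site (randomization is blocked by clinic). Where surveys are partly missing, use a mixed model that constrains the two arms to a common baseline mean, so that people with only one of the two surveys still contribute.
- Apply the same approach to the other survey domains if they are to be analysed in the same way, and say so.
- For binary or ordinal items, use a baseline-adjusted model and report a marginal risk difference, so that the estimand stays comparable with a difference in proportions. For ordinal items, name the response cut-point in advance.
- Keep difference-in-differences as a sensitivity analysis.

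The cost is small: a short SAP edit and the work of defining the score. No new data are needed.

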| Evaluate the implementation and effectiveness of a multicomponent AI clinical intervention on DR screenings, early stages of DR detection, and referrals to the specialist for follow up on abnormal results. | 
 
1. Completion of DR screening. Data will be obtained through EHR at the time of the enrollment (baseline).
 
2. Results of the DR screening: for usual care specific diagnosis; for intervention group defined as normal, mild-to-moderate DR (mtmDR), visual threatening DR (vtDR) or ungradable. Data will be obtained through EHR at the time of the enrollment (baseline) and over the duration of the study.
 
3. Referral to specialist completion status and final diagnosis. Data will be obtained through EHR over the duration of the study.
 
 | 
To evaluate the effectiveness of the clinical intervention will be tested using a RCT (Aim 2), with the “intervention group”, which is characterized by 1) conducting autonomous DR screening system (H2.1) with 2) integration of the results into the EHR (H2.2). The “usual care” group represents the existing primary care model, which involves medical visits, referral to the specialist for a DR screening, and follow-up.
 
In addition, to evaluating the impact and efficiency of the POC-AI System we will also collect AI system data, number of orders submitted, screenings completed (images), number of ungradable and time of attempts, time the patient spent in front of the camera.
 |

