#### 6.1.1 STUDY INTERVENTION DESCRIPTION

The purpose of the DRES-POCAI research study is to improve eye care by using a special camera and a computer system called EyeArt® to make diabetic eye screenings faster and more accessible. Eligible participants that choose to participate will complete a survey about diabetes management and eye health. They will also be randomized and assigned to one of the two study groups: usual care (receive a retinal screening by an eye care provider) or intervention group (receive a retinal screening using a special camera and EyeArt®). The study visit (baseline) is expected to be completed in a period of ~60 minutes.

During the first study visit, participants will:

1. Complete informed consent
2. Fill out a survey on diabetes, eye health, and barriers to retinal screening completion.
3. Undergo randomization and be assigned to a study group: usual care or intervention.
4. Undergo DR Screening. *Intervention group* participants will complete the DR screening using a special camera and the artificial intelligence (AI) system (EyeArt®) on the same day of the study

visit. Participants will also complete a satisfaction survey related to the use of EyeArt system to complete their DR screening.

*\*\*Usual care group* participants will complete the DR screening with an eye care provider on a different day and at a different location. The study staff will assist in scheduling appointments for the DR screening to ensure the completion of this important component.

5. Health Education Overview and Engagement materials: at the end of the study visit, the study staff will provide participants with an overview of the health education sessions. Staff will also ensure participants have scheduled any/all follow-ups. Participants will receive educational materials about diabetes care and management, eye health, etc.

Complete medical visit: Participants will complete a medical visit on the same day as the study visit (for in-person visits). If the medical visit is via telehealth, then participants will complete it on a different day after the screening.

Follow up contact with participants: After the first (baseline) study visit, all participants will participate in one 20-minute educational session and complete a short survey within 6 months of the baseline. Upon the completion of the second health education session and the 6-month follow-up survey, participants will receive a \$25 gift card.

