- c) Employing statistical methods to adjust for potential biases, such as sensitivity analysis to address differences between treatment groups. These measures collectively strengthen the reliability and credibility of the study outcomes.

Regarding control group expectations, participants in the usual care group may be less motivated to seek external eye exams knowing the immediate screening results are not available during the study. The study will emphasize the importance of comprehensive eye exams in both groups to mitigate this. In addition, both usual care and intervention groups will receive health education materials and care coordination support, this is anticipated to increase engagement for participants in the usual care group.

By implementing these measures, the study team will minimize bias in randomization and enhance the validity and reliability of study results, addressing the absence of blinding.

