#### 9.4.1 GENERAL APPROACH

**Descriptive Statistics:** Categorical data will be presented as frequencies and percentages. Based on normality assessments, continuous data will be presented as means (standard deviations) or medians (interquartile range). Patient characteristics will be presented using descriptive statistics and compared between intervention and standard of care groups using two-sample t tests for continuous (normally distributed) variables and Pearson's chi-squared test will be used for binary and categorical variables.

**Inferential Tests:** The impact of the intervention will be assessed by comparing the outcome of interest between intervention and usual care groups using logistic or poisson regression (depending on distribution of outcome) and adjusting for identified covariates and assessing study intervention arm as the primary independent variable. A significant level (p-value) of 0.05 will be used with 95% confidence intervals reported. Two-tailed tests will be conducted unless there is a strong a priori basis for a one-tailed test.

**Covariates:** Covariates will be assessed individually between intervention and usual care groups and by outcome of interest. We will use Hosmer and Lemeshow's covariate inclusion approach (purposeful selection at each modeling step) when developing models to ensure inclusion of biologically and statistically relevant variables.

**Assumptions:** Data will be checked for normality of distribution prior to analysis. If assumptions are violated, appropriate transformations will be applied, or non-parametric tests will be used.

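### The primary outcome is read from the SYHealth record, which may capture later, off-site usual-care exams less completely than in-clinic AI screens, and Section 3 dates the data pull at enrollment

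*Combined protocol and SAP*

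**What the plan says.** **Source and coding.** Protocol Section 1.1 (Description of Study Intervention) takes screening uptake from the EHR. Section 10.1.7.1 and the SAP's Data Management section agree. Section 9.4.2 codes completion as Yes or No, with no level for unknown. The SAP rules out imputing outcomes.

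**Timing of the pull.** The first endpoint in the Section 3 table reads "Completion of DR screening. Data will be obtained through EHR at the time of the enrollment (baseline". The next two endpoints in that table, screening results and referral completion, are collected over the duration of the study.

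**Outcome window.** This is 60 days from randomization in Section 9.4.2 and 3 months in the SAP's Outcome Measures.

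**Where the exams happen.** In the intervention arm, study staff take the images in clinic on the day of the study visit, and the result can be opened inside the SYHealth EHR (Sections 1.1, 4.4, 6.1.1). In usual care, "participants will complete the DR screening with an eye care provider on a different day and at a different location" (Section 6.1.1). Section 1.1 says that these exams are scheduled under SYHealth's own procedures and that the optometrist enters the result in the medical record. Section 6.3 warns that "participants in the usual care group may be less motivated to seek external eye exams".

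**Returned results.** For an exploratory comparison of AI results with specialist diagnoses, the SAP (Statistical Methods, Exploratory analysis) says that only data on intervention participants with ungradable or abnormal AI results "who were examined by an eye specialist and had results returned to the SYH will be available for comparison".

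**Other contacts.** Staff help usual-care participants to book. Section 8.1 states that "Baseline and follow-up surveys will encompass the baseline and 6-month follow up surveys"; the domains it names are knowledge and beliefs, self-efficacy, and self-management. Neither document describes a way to learn of exams done elsewhere, or a rule for an exam whose report never arrives.

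**The concern.** In an EHR query, an exam that was done but not recorded looks the same as an exam that was never done. With Yes/No coding and no unknown level, it becomes a No. Few intervention participants are exposed to this, because their screen is produced in clinic at the study visit. Nearly all usual-care completions depend on an entry made later, at another place, by someone else. Any shortfall in that chain lowers the recorded control rate and favours the intervention.

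The pull date makes this more than a theoretical worry. Randomization and the AI screen take place at the enrollment visit, and the usual-care exam takes place on another day. A pull dated at enrollment can see the first and cannot see the second.

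Section 6.3 relies on screening rates being an objective outcome to offset the lack of blinding. That protection weakens if the chance of an exam being counted depends on the arm.

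**Working it through.** **1. The plan's own figure.** Inputs: 59% versus 69% and 1:1 allocation (SAP, Sample Size and Power Calculations and Randomization); "All statistical tests will be two-sided unless defined otherwise" (SAP); "A significant level (p-value) of 0.05 will be used with 95% confidence intervals reported" (Section 9.4.1); and, for power and size, "of 0.8 (power), we estimated that the target enrollment to detect this difference is 722 participants (361 per arm" (SAP, where 0.8 is labelled as beta but glossed as power).

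n per arm = [1.960 × √(2 × 0.64 × 0.36) + 0.8416 × √(0.59 × 0.41 + 0.69 × 0.31)]² / 0.10² = 360.5, so 361 per arm and 722 in total. The stated figure reproduces and is not in dispute.

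**2. Effect of unrecorded exams when there is no true difference.** Let u be the share of completed usual-care exams that never reach the record. The documents give no value for u; 5% and 10% are assumptions. Take true completion as 59% in both arms and AI capture as complete.

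- Recorded control rate = 0.59 × (1 − u). False gap = 0.59 × u.
- SE0 = √(2p̄(1 − p̄)/n), where p̄ is the mean of the two recorded rates. SE1 = √([p₁(1 − p₁) + p₂(1 − p₂)]/n).
- Chance of significance favouring the intervention = 1 − Φ((1.960 × SE0 − gap)/SE1). The opposite tail is added for the two-sided rate.

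For u = 5%: control 0.5605, gap 0.0295, SE0 0.03679, SE1 0.03678, z = 1.159, upper tail 12.3%, lower tail 0.3%.

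For u = 10%: control 0.531, gap 0.059, SE0 0.03694, SE1 0.03688, z = 0.364, upper tail 35.8%, lower tail below 0.1%.

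| u (assumed) | False gap | Two-sided false-positive rate, 361 per arm | Same, 424 per arm |
|---|---|---|---|
| 0 | 0 | 5.0% | 5.0% |
| 5% | 3.0 points | 12.6% | 14.0% |
| 10% | 5.9 points | 35.8% | 40.9% |

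A larger sample makes the error more likely, because it is a bias.

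**3. If the planned effect is real.** With true rates of 59% and 69%, the recorded difference grows from 10.0 points to 13.0 (u = 5%) or 15.9 (u = 10%). The odds ratio grows from 1.55 to 1.75 or 1.97.

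**4. If 59% is already a recorded rate.** True usual-care completion would then be 0.59/(1 − u), which is 62.1% or 65.6%. With that same true rate in both arms and full AI capture, the false gap is 3.1 or 6.6 points and the two-sided rate is 13.7% or 44.3% (361 per arm).

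**5. Intervention participants examined elsewhere.** If a share s of intervention completions also depends on later documentation and suffers the same loss, the net gap is 0.59 × u × (1 − s). It vanishes only if s reaches 1.

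These are unadjusted normal approximations. The planned logistic model would give somewhat different values.

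**The case against.** The strongest reply is that the usual-care route is a recorded one. Section 1.1 has the optometrist document the result, staff help with booking, and Section 6.4 has the Data Analyst report on appointment outcomes. A different location need not be outside the SYHealth network, and in Section 6.3 external may mean only outside the study visit. This stands as a reason why u could be small. It does not cover exams done elsewhere.

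A second reply is that no rule says an absent record is scored as No. The only explicit rule of that kind appears to be the SAP's handling of missing results for the diagnosis outcome. That is correct; the coding is inferred. But deleting everyone without a record would leave 100% completion in both arms, so No is the only workable coding.

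A third is that the survey instruments, the SOPs and the authorization form were not available. Section 6.1.1 has the baseline survey also cover barriers to screening, so the Section 8.1 list of domains is not exhaustive. A question on outside exams may exist.

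A fourth is that 59% may already be a recorded rate. Panel figures in Section 1.1 give about 24,000 × 13% + 9,000 × 14% = 4,380 patients with diabetes, and the 2,514 screened in Section 9.2 are 57% of them. This is suggestive only. Step 4 of the working shows that the conclusion does not turn on it.

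A reader might also infer from the SAP's remark on returned results that the authors concede losing usual-care exams. They do not. The remark concerns intervention participants with abnormal or ungradable AI results in an exploratory comparison.

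**Conclusion.** The concern holds as a risk of unequal capture, and it should be fixed. Three things come from the text: the EHR is the stated source of completion, the two arms are screened at different times and places, and the Section 3 pull date cannot capture usual-care exams and conflicts with both stated windows. Two things are inference: that an unrecorded exam is scored as No, and that some usual-care exams go unrecorded.

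The direction, if there is a loss, favours the intervention. The size is unknown. The 13% and 36% false-positive rates hold only under the assumed 5% and 10% losses, with equal true completion and complete AI capture.

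Stronger readings are tempting and are not supported. The documents do not show that AI screens are always captured; they say that results can be opened in the EHR. They do not show that only one arm is affected, since an intervention participant examined elsewhere faces the same loss. A loss of 17% would produce the whole target difference (0.59 × 0.17 = 10.0 points), but that value is chosen to do so and nothing in the documents points to it. Nor is it likely that the enrollment pull is the working rule, since nearly every control would then fail. It is wording that has to be reconciled.

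**What to change.** 1. Reconcile the 60-day and 3-month windows. Replace the enrollment pull for completion in Section 3 with one EHR extraction, run in both arms after that window closes. Allow the same pre-stated lag in both arms for late reports, and count exams by date of service, not by date of entry.
2. State in Section 9.4.2 and the SAP how an exam without a record is coded in the primary analysis.
3. Add one item to the existing 6-month survey in both arms: any eye exam since enrollment, where and when.
4. Add a sensitivity analysis that also counts self-reported exams dated within the window. Request outside reports only where the signed authorization allows it.

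The cost is a later query, one survey item and a little data work, with no new visit. Self-report brings recall error into an open-label trial, which is why it belongs in the sensitivity analysis and not in the primary outcome. The recorded control rate may rise and the estimated effect may shrink. If few exams prove to be unrecorded, the same steps will show it.
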